## Abstract

**Background:**

There is a high association between disturbed (poor quality) sleep and depression, which has lead to a consensus that there is a bidirectional relationship between sleep and mood. One time in a woman’s life when sleep is commonly disturbed is during pregnancy and following childbirth. It has been suggested that sleep disturbance is another factor that may contribute to the propensity for women to become depressed in the postpartum period compared to other periods in their life. Post Natal Depression (PND) is common (15.5%) and associated with sleep disturbance, however, no studies have attempted to provide a sleep-focused intervention to pregnant women and assess whether this can improve sleep, and consequently maternal mood post-partum. The primary aim of this research is to determine the efficacy of a brief psychoeducational sleep intervention compared with a control group to improve sleep management, with a view to reduce depressive symptoms in first time mothers.

**Method:**

This randomised controlled trial will recruit 214 first time mothers during the last trimester of their pregnancy. Participants will be randomised to receive either a set of booklets (control group) or a 3hour psychoeducational intervention that focuses on sleep. The primary outcomes of this study are sleep-related, that is sleep quality and sleepiness for ten months following the birth of the baby. The secondary outcome is depressive symptoms. It is hypothesised that participants in the intervention group will have better sleep quality and sleepiness in the postpartum period than women in the control condition. Further, we predict that women who receive the sleep intervention will have lower depression scores postpartum compared with the control group.

**Discussion:**

This study aims to provide an intervention that will improve maternal sleep in the postpartum period. If sleep can be effectively improved through a brief psychoeducational program, then it may have a protective role in reducing maternal postpartum depressive symptoms.

**Registration details:**

This trial is registered with the Australian New Zealand Clinical Trials Register under the registration number ACTRN12611000859987

## Background

On average, one third of a person’s life is spent asleep [1]. Sleep is vital, allowing the body to rest, replenish resources in the brain and body [2], and consolidate new information [3]. Since the 1960s, sleep duration has declined [4,5], complaints about sleep problems have almost doubled [6] and many individuals report poor sleep quality or consistently insufficient sleep at night [7]. For example, approximately 30% of the Australian population report sleeping for less than 6.5 hours per night [8]. Partial sleep deprivation (consistent short sleep) in humans is associated with hypertension, impairment of glucose control, weight gain [7], reduced concentration, irritability and depression [9]. The various consequences become apparent at different stages of partial sleep deprivation, with reduced cognitive performance and poor mood appearing after just one night of less than 5 hours of sleep [9]. Further, untreated sleep disturbance is known to lead to depression while depression can also precipitate sleep disturbance [10]. It is currently unclear whether disturbances to sleep most often precede mood disturbance or whether depression typically precedes sleep disturbance. There is consistent evidence to indicate that irrespective of the order of onset, sleep disturbance and depression are highly associated [11,12]. Sleep disruption is very common in depression and is one of the symptoms described by the Diagnostic and Statistical Manual of Mental Disorders – fourth edition in the diagnosis of depression [13]. Depression has also been shown to precede sleep disturbance and that with increased insomnia severity; the likelihood that the individual had a prior history of a mental disorder is greater [14]. On the contrary, some studies found sleep disturbance precedes the depression in most cases [15]. For example, patients with insomnia are nearly 10 times more likely to develop depression than those without sleep complaints or whose insomnia had resolved [16,17]. Further, in a prospective study, the risk of developing major depression over twelve months was higher in individuals who had insomnia compared with those who did not. This risk was reduced if the insomnia resolved during the year [18]. This research would suggest that insomnia can be seen as a risk factor for the onset of a depressive episode [18,19]. The literature has currently not established the direction of causality; however, it is highly likely that the relationship is bi-directional. Therefore, any period where sleep is likely to be compromised is potentially a high risk time for the development of depression, setting up a vicious cycle of depressed mood and poor sleep.

Sleep is commonly disturbed during pregnancy and following childbirth [20]. Even individuals who have been ‘healthy sleepers’ prior to pregnancy will notice a change in their sleep patterns during pregnancy [21]. There are many physiological, psychological and lifestyle changes that occur during this period. Pain or discomfort while trying to sleep, and more frequent night-time toilet visits are common. Many women experience symptoms of insomnia, whilst some develop restless leg syndrome [22] and/or sleep apnoea [23]. Pregnancy requires adaptation to an ever-changing body and unfamiliar sleep patterns. As pregnancy progresses, complaints of sleep disruption become more prevalent [24] and sleep quality deteriorates significantly [25]. The most common sleep difficulties during pregnancy are frequent night wakening, difficulty falling asleep and waking too early. In fact, the vast majority of women (92%) report restless sleeping [26]. As a result, particularly if labour onset is at night or labour continues overnight, many women begin motherhood sleep deprived.

Sleep disturbances are common to all new mothers. The sleep patterns of new mothers are characterised by shorter sleep durations at night resulting in daytime fatigue [27,28]. This is particularly marked for first time mothers, who have lower sleep efficiency, spend more time in bed and have a greater wake after sleep onset during pregnancy than multiparous mothers [29]. These mothers also have fewer sleep episodes in the early postpartum period and generally poorer sleep quality than their multiparous counterparts [29,30]. The high rates of sleep disturbance amongst new mothers is not surprising given the many physical, lifestyle, psychological and emotional changes that occur following childbirth. During the first few days after childbirth, the breasts begin to produce milk, which is new and often uncomfortable. Genital, pelvic [31] and back pain [32] are also common after childbirth, which is known to further disturb sleep [33]. In addition to the physical changes, lifestyle changes and parenting responsibilities also contribute to the potential for sleep disruption. New infants sleep for short bursts, which gradually lengthen with time; but they generally do not sleep through the night for more than 5–6 hours before 6 months of age [34]. Hence, in addition to all the physical postpartum reasons for sleep to become interrupted, motherhood brings frequent, unavoidable night time wakening to attend to the baby’s needs. It has been suggested that sleep disruption may be one factor that contributes to a greater likelihood that women will become depressed in the postpartum period compared to other periods in their life [35]. However, there are surprisingly few studies that have investigated the relationship between sleep and PND.

Those studies that have assessed sleep and depression in the postpartum period, have confirmed strong associations [27], indicating that depressed mothers had poorer sleep quality, more sleep disturbance and more daytime sleepiness compared with non-depressed mothers. While there are few prospective studies, difficulty falling asleep or staying asleep predict PND [36]. Further, interventions that improve infant sleep patterns tend to see an improvement in maternal mental health although the cause and effect have not been confirmed [37,38]. If sleep disturbance can, in some cases, precede and even cause depressed mood amongst women during the postpartum period, then a sleep-focused intervention may have a role to play in preventing the development of mood disorders. However, there have been no investigations of the efficacy of interventions in the pre-natal period targeting both infant and postnatal maternal sleep.

Currently, there are a number of programs that exist to educate and prepare couples for childbirth and parenthood. The majority of programs educate parents-to-be about the practical and physical aspects of childbirth. While we were unable to find any programs with a major focus on sleep that occur prenatally, we did find a study examining a sleep intervention that occurs in the first few days following childbirth [39]. This study was conducted in Canada and randomised 30 new mothers to either an intervention or a control group. The intervention consisted of a private 45min consultation with a nurse which covered sleep hygiene, relaxation, strategies for increasing maternal sleep, acknowledgement of the challenges of parenting and sleep disruption, and details about infant sleep. They then received a booklet about sleep and had weekly phone calls for the first 5 weeks. The control group met the nurse for 10minutes, received a pamphlet about sleep and phone calls at 3 and 5 weeks postpartum. Outcomes for this study included questionnaires at baseline and 6 weeks postpartum as well as sleep diaries and actigraphy at 6 weeks postpartum. Results indicated an average of an extra 57 minutes of nighttime sleep in the intervention group than the control group. Fewer participants in the intervention group rated sleep as a problem than those in the control group and infants in this group had fewer night wakenings and longer nighttime sleeps than those in the control group. Despite the small sample size and limited power, the findings from this study are promising. As we were not able to find any large randomised controlled trials that occurred prenatally with a focus on sleep, the aim of this study is to bridge that gap.

This research will test the efficacy of a novel, brief sleep intervention for women during their final trimester of pregnancy using a cluster randomised design. The purpose of the intervention will be to educate women about what to expect in their sleep and their new baby’s sleep and how to adapt to these changes to reduce their sleep loss and manage their sleep better. We hypothesise that the intervention will result in improved scores on the primary outcomes, including sleep quality, sleep management and daytime sleepiness compared with the control condition. If the intervention is successful in improving sleep outcomes, we would expect that there would also be better outcomes observed in the mood of participants receiving the intervention.

### Aims and objectives

The aims of this study are:

1. To determine whether a sleep focused psychoeducational intervention delivered pre-natally can lead to better sleep outcomes for both mothers and infants during the post-natal period.

2. Given that insomnia and sleep disturbance can precipitate depression [40], if the sleep intervention does lead to better sleep outcomes in the postpartum period, we would like to determine whether this will reduce the likelihood of experiencing depressive symptoms.

### Hypotheses

1. Women who receive the sleep psychoeducational intervention will have better outcomes 6 weeks, 4 months and 10 months following delivery than those who do not receive the intervention on the following primary outcomes.

(a) Sleep quality – measured by the PSQI

(b) Sleep patterns – measured by shorter night wake periods indicated by the mother and infant sleep diary

(c) Self-efficacy – measured by the general self-efficacy

2. If changes in sleep, consistent with hypothesis 1(a,b) are observed, we would also expect that women who received the intervention will have fewer depressive symptoms at 6 weeks, 4 months and 10 months postpartum than the control group.

The PSQI is our primary outcome, which is a scale consisting of itemised scores which are likely to be affected differentially by pregnancy and motherhood. During pregnancy, the most common causes of disrupted sleep include the need to urinate, uncomfortable position, aching in a position, and being too hot or cold [26]. These common issues predominantly contribute to Item 5 and following the birth of the baby are generally normalised or reduced. With motherhood, women are woken several times during the night by the baby’s needs, and may develop different difficulties within Item 5. Sleep tends to deteriorate or remain unchanged for women as measured by the total PSQI. We expect this intervention will improve sleep outcomes relative to the control group.

### Outcomes and treatment effect

#### Primary outcomes

1. Mothers’ sleep quality indicated by:

• Pittsburgh Sleep Quality Index (PSQI)

• Insomnia Severity Index (ISI)

2. Mothers’ sleepiness indicated by:

• Multidimensional Assessment of Fatigue (MAF)

• Epworth Sleepiness Scale (ESS).

3. Sleep patterns: Sleep diaries and a Generic Sleep Questionnaire will help determine sleep patterns in the mother. This will indicate whether participants who receive the intervention have more consistent sleeping patterns or get more sleep than those in the control group or if the potentially different scores on the questionnaires are attributed to their ability to manage these changes better.

4. Actigraphy Measures

• Objective sleep-wake hours and patterns.

#### Secondary outcomes

1. Mothers’ depressive symptoms indicated by:

• Edinburgh Post Natal Depression Scale (EPDS)

• Depression, Anxiety and Stress Scale (DASS)

#### Process measures

There were a series of measures included in order to try and ascertain the mechanisms of treatment outcome. These are explained below:

1. Bonding between a mother and infant has high associations with poor sleep and low mood. Therefore a measure of bonding using the Being a Mother and Bonding Scale (BaMB) will be administered.

2. Coping skills mediate the relationship between stress and sleep [41] and are therefore an important measure to consider. We shall be assessing coping strategies using the Brief Coping Scale.

3. Infant temperament can have a profound effect on sleep opportunities for mothers. We shall control for this effect by measuring infant temperament with the Infant Characteristics Questionnaire.

4. The General Feeding Questionnaire includes night-time feeding patterns; which can often affect sleep.

## Methods

### Study design

This study will be a cluster randomised controlled trial. Participants will be recruited from consecutive attendees at prenatal classes at the Royal Prince Alfred Hospital (RPAH), Sydney Australia. In addition, the study is being advertised in obstetrician’s offices, and through the Study Facebook Page. Hence we will also accept self-referrals from these sources or from recommendations from friends. Participants from the same prenatal class will be randomised as a group in order to avoid contamination effects. The minimum in a cluster will be 3 and the maximum per cluster will be 10. Any participants from a group where less than 3 people consent or more than 10 people consent will join the next randomised cluster. Additional participants will join the clusters formed by the participants from RPAH based on the date they are recruited.

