#### Recruitment from Facebook.com

In order to maximise recruitment, a Facebook page was published, facilitating participants to ‘share’ or recommend the study with other potential participants as well as allowing interested individuals to access the information and volunteer themselves as participants. The link to the active Facebook page as well as a screen shot of the page and the pictures presented on the page can be found in Additional file 1: Figure S2: *Facebook Page ‘Sleep for New Mums’.*

#### Time 1

Participants will be called by the study coordinator. The study will be explained and medical history, demographics and other relevant information will be collected. If the individuals are eligible, they will be asked to provide informed consent and complete the set of baseline questionnaires.

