#### Randomisation

Envelopes have been prepared and sealed by an independent researcher. Each enveloped is labeled ‘Cluster1’ (C1), ‘Cluster2’ (C2) etc.… Once a minimum of 3 and a maximum of 10 participants have been screened and completed the *Time 1* components, they will be allocated into a cluster and an envelope will then be opened to reveal whether the participants in that cluster will receive intervention or control condition.

#### Time 2

Participants will receive a phone call from the study coordinator 3 weeks following the birth of the baby. For the intervention group, this is when potentially bad habits may start to form and as such we aim to remind the participants of the intervention and its content. For the control group, the phone call will be simply to provide support, which might otherwise vary between the groups.

#### Time 3

Six weeks after delivery, participants will be contacted by phone. The phone call will be scripted involving questions about sleep hours and patterns as well as courtesy questions about how they are managing. Participants in the intervention group will receive an additional segment of the script reminding them to look through the notes provided during the program and offering advice and support if necessary. We shall explore what has or has not been useful for them and direct them to the relevant section of their notes to review. We will also allow them to ask any questions they may have about sleep. At this stage, all participants will complete the online questionnaires once again. These questionnaires will include the baseline and post-delivery questionnaires.

#### Time 4

Approximately 4 months after delivery, participants will fill out the baseline and post-delivery questionnaires again.

#### Time 5

10 months after delivery; participants will fill out 2 questionnaires about sleep (PSQI & ISI), 2 about depression (DASS & EPDS) and the sleep and feeding questionnaires. This will conclude their participation in the study. A flowchart of the procedure can be seen in Figure 1.

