### Statistical considerations

Power is difficult to calculate given that only one study has attempted to intervene in sleep in the pre or postnatal period. That intervention was delivered early in the postpartum period. The authors found a large effect size on both sleep duration (ES = 1.15), and depressive symptoms using the Edinburgh Postnatal Depression Scale (ES= 0.78) [39]. It is unclear whether a preventative program would achieve such large effect sizes. However, studies in individuals with insomnia attending a sleep intervention have consistently found effect sizes in the 0.4 – 0.8 range [48,49]. Hence, we chose the smallest of these effect sizes in order to be conservative. This was particularly important as the effect sizes we have taken into consideration were shown in interventions that treated people for insomnia, which one would expect to have a greater effect than a preventative program wherein the sample begins at a baseline level. The effect sizes (Cohen’s d) from past sleep programs using the sleep questionnaires of the current study (the PSQI and ISI) has ranged from 0.35 – 0.88 [50]. On the basis of these in order to achieve 80% power, based on the most conservative effect size, we would need only 41 participants per group to achieve significance at 0.05 level. However, the cluster design increases the sample size requirement according to the following formula: 1 + (*m* – 1)*ICC, where ICC is the intra-cluster correlation, (the correlation between patients’ scores within each group) and *m* is the average number of patients per group. We could not find any published studies, using the sleep measures and reporting ICCs. Therefore, we based our assumptions on ICCs reported for mood variables. Again, we could not find any for EPDS, however, Adams et al. (2004) [51] published 1039 ICCs from 31 studies and found the median value to be 0.01 for the HADS (interquartile range [IQR] 0 to 0.032, range 0 to 0.840). We aim for an average group size of 6, and to be conservative took the mean for the ICC of 0.42, requiring 2.6 times the number of participants. Therefore to ensure sufficient power to find differences on quality of life at an effect size of at least 0.4, we need 107 participants per group (n=214).

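### Friends referred by participants join clusters by recruitment date alone, so linked women can fall in opposite arms; the resulting dilution is of unknown and possibly small size

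*Protocol article*

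**What the plan says.** The protocol article gives a reason for cluster randomisation under Study design: "Participants from the same prenatal class will be randomised as a group in order to avoid contamination effects". The same section adds recruitment through obstetricians' offices and Facebook, and continues: "Hence we will also accept self-referrals from these sources or from recommendations from friends". Under Recruitment from Facebook.com, the page is described as "facilitating participants to ‘share’ or recommend the study with other potential participants".

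Women who do not come from the hospital classes are assigned by one criterion: "Additional participants will join the clusters formed by the participants from RPAH based on the date they are recruited".

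Under Randomisation, once 3 to 10 women have completed Time 1, "they will be allocated into a cluster and an envelope will then be opened to reveal whether the participants in that cluster will receive intervention". The other possibility is the control condition. Each cluster has its own envelope. Statistical considerations plans equal groups of 107 (214 in all), an average cluster size of 6 and an effect size of at least 0.4.

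**The concern.** The protocol treats contact between women as a route of contamination and guards against it for women of one class. The referral route brings in women who know each other by definition, and the assignment rule for them takes no account of that link. A woman whose friend joins later may find that the friend's cluster has drawn the other arm.

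What is tested is largely information: two evening sessions plus notes that intervention women are reminded to reread at the six-week call. Such material passes easily between friends who are expecting or have just had a baby. If it reaches a control woman, the contrast between the arms shrinks and the estimated effect is biased towards no difference.

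**Working it through.** No stated figure is in dispute, so the check is mainly a reading of the rules in order, followed by illustrative arithmetic.

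**Can linked women be separated?**

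1. A friend may enter on a recommendation (Study design), and participants are named among those who may recommend (Recruitment from Facebook.com).
2. A friend from outside the classes is placed by recruitment date (Study design).
3. If her referrer's cluster is still forming, she may land in it. Both women then share one envelope, and the chance of opposite arms is 0.
4. If that envelope has been opened, she must join a later cluster with its own envelope.
5. The sessions are prenatal, so the envelope is opened before delivery, and follow-up runs to 10 months after it. Recruitment is planned over 1.5 years. Most of a participant's time in the trial therefore falls under step 4.

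**Chance of opposite arms when the clusters differ.** Inputs: 214 women and an average cluster size of 6.

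- Number of clusters: 214 / 6 = 35.7, about 36.
- Independent 1:1 allocation: 50%.
- Envelopes balanced 18:18 (an assumption): 18 / 35 = 51%.

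**What dilution would look like.** Let c be the share of controls who gain the full benefit through a friend. The article does not give c, so the values are assumptions. The diluted effect is 0.40 × (1 − c), and the sample needed to hold power is multiplied by 1 / (1 − c)².

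| c | Controls out of 107 | Effect | Sample multiplier |
|---|---|---|---|
| 5% | 0.05 × 107 = about 5 | 0.40 × 0.95 = 0.38 | 1 / 0.95² = 1.11 |
| 10% | 0.10 × 107 = about 11 | 0.40 × 0.90 = 0.36 | 1 / 0.90² = 1.23 |

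If only half the benefit were passed on, the effect would be 0.40 × (1 − 0.5c): 0.39 at 5% and 0.38 at 10%.

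**How many late referrals that implies.** Each cross-arm pair contains one control. If a share s of the 214 women are referred after their referrer's envelope is opened, and half of them land in the other arm, the exposed controls number 0.5 × 214 × s = 107s. So c equals s at most. A c of 5% to 10% needs about 11 to 21 such referrals, with no control counted twice.

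The value of 0.4 is taken as stated; how the 214 was derived is a separate matter.

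**The case against.** Several stronger readings are tempting, and the article does not support them.

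- A reader might infer that enrolled women are urged to recruit their friends. The text says only that the page makes sharing possible, and the friends mentioned under Study design need not be participants, let alone randomised ones.
- A reader might infer a contradiction with the purpose of clustering. The stated purpose covers women of one prenatal class. Friends were not promised that protection, so this is a gap in the safeguard.
- A reader might assume that a large share of the sample is affected. Hospital classes are the core source, and a friend must herself be a first-time mother in the third trimester without a history of major depression. Nothing supports a share as high as 40%, or any particular fraction of benefit passed on. Controls already receive the same booklets (Intervention), so only session content and notes can leak.
- A reader might conclude that friends of randomised women should be excluded. That would cost at least as much information as the dilution. Assume half the benefit is transferred and the excluded women are not replaced. At s = 40%, dilution leaves 214 × 0.8² = about 137 effective women and exclusion leaves 214 × 0.6 = about 128. At s = 10% both leave about 193. Challenges already names recruitment and attrition as the main difficulty.
- A reader might add that a referrer colours her friend's self-reported answers. No part of the article addresses this, and it belongs to blinding in general.

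It is also fair to say that the Time 1 call collects further relevant information, which might include the referral source; a condensed article would not list every item. All of these limits stand. They do not remove the central fact: the assignment rule is stated, it uses date alone, and it can separate women who are known to be linked.

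**Conclusion.** The point holds as a minor but worthwhile correction. A friend recruited after her referrer's envelope is opened has about a 50% chance (51% with balanced envelopes) of being in the opposite arm, and no stated rule prevents or accounts for this. The bias is towards no difference, so it threatens a false null and would not create a spurious benefit.

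The size cannot be fixed from the article. An effect of 0.38 to 0.36 in place of 0.40 assumes that 5% to 10% of controls gain the full benefit; with less sharing or fewer late referrals the loss is smaller. The conclusion rests on three assumptions: some recommenders are participants, some of their friends are recruited after allocation, and some session content is passed on.

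**What to change.** Four changes, applied from now on, since Trial status reports that recruitment is in progress:

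1. At the Time 1 call, ask each self-referred woman whether she knows an enrolled participant, and record the link.
2. If that participant's envelope is unopened, place both women in the same cluster, within the limit of 10, in place of the date rule.
3. Do not direct requests to share or recommend the study at women already randomised.
4. If the envelope is already open, randomise the friend as planned, and add a sensitivity analysis that omits linked women in opposite arms. Treat it as supportive only, because willingness to recommend the study may depend on the referrer's arm.

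The cost is one extra question, slight extra administration and possibly a few fewer referrals. Links formed before the change cannot be undone, but they can be asked about at the next scheduled contact and included in the sensitivity analysis.

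### The sample size formula uses only the average cluster size although clusters may hold 3 to 10 women, so the design effect is understated; this adds modestly to a power shortfall that has other main causes

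*Protocol article*

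**What the plan says.** All references are to the protocol article.

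- **Cluster size.** Study design sets the limits: "The minimum in a cluster will be 3 and the maximum per cluster will be 10". The Randomisation section repeats them. Women from classes with too few or too many consenters move to the next cluster, and self-referred women are added as well: "Additional participants will join the clusters formed by the participants from RPAH based on the date they are recruited".
- **Sample size formula.** Statistical considerations prints the inflation factor 1 + (m - 1)*ICC, in which m "is the average number of patients per group", and adds: "We aim for an average group size of 6". There is no term for variation in size.
- **Inputs and result.** The unclustered requirement is given as 41 per group for 80% power at the 0.05 level. For the clustering, the authors "took the mean for the ICC of 0.42, requiring 2.6 times the number of participants". The conclusion is that "at an effect size of at least 0.4, we need 107 participants per group (n=214").
- **Analysis.** The Data analysis plan describes a linear mixed model. The only random effect it lists is for subjects.

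**The concern.** The formula 1 + (m - 1)*ICC is exact when all clusters have the same size. When sizes vary and each woman counts equally, large clusters contribute more correlated pairs than small clusters save. The factor then becomes 1 + ((1 + CV^2)*m - 1)*ICC, where CV is the standard deviation of cluster size divided by its mean. Since CV^2 cannot be negative, a formula that uses only the mean can understate the factor but never overstate it. The extra term is CV^2 * m * ICC, so it grows with the ICC, and this plan chose a large one.

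At stake is whether the stated design effect and power describe the trial as laid out. The article calls its sample size conservative; leaving out this term works in the opposite direction.

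**Working it through.** **Inputs from Statistical considerations:** d = 0.4 (SD = 1), alpha 0.05, 80% power, 41 per group before clustering, m = 6, ICC 0.42, stated factor 2.6, 107 per group. **From Study design:** sizes 3 to 10.

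**Assumptions:** two-sided test (sidedness is not stated), normal approximation, no attrition. The CV is not given, so a range is used, with mean 6 and limits 3 and 10:
- range/4 rule: SD = (10 - 3)/4 = 1.75, CV = 1.75/6 = 0.29
- maximum-entropy distribution on 3 to 10 with mean 6: CV = 0.38 (0.376 unrounded)
- extreme, every cluster either 3 (share 4/7) or 10 (share 3/7): variance = 9*4/7 + 16*3/7 = 12, SD = 3.46, CV = 0.58

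**Step 1: the plan's own figures.**
- 41 * 2.6 = 106.6, rounded up to 107. This product reproduces.
- 41 does not follow from d = 0.4: n = 2*(1.96 + 0.84)^2/0.4^2 = 98.1, so 99 per arm (78 one-sided). 41 per arm corresponds to d of about 0.62.
- 2.6 does not follow from m = 6 and ICC 0.42: 1 + 5*0.42 = 3.10. A factor of 2.6 needs ICC 0.32 at m = 6.

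**Step 2: power with equal clusters of 6.** The effective n per arm is 107/DE, where DE is the design effect, and power = Phi(0.4*sqrt(n_eff/2) - 1.96).
- Stated factor 2.6: n_eff = 41.2, power 44%.
- Factor 3.10: n_eff = 34.5, power 38%.

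The shortfall is therefore present before any variation in size is considered.

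**Step 3: add unequal sizes at ICC 0.42.** DE = 3.10 + CV^2*6*0.42. For an analysis that weights clusters efficiently, DE = 3.10/RE, where RE = 1 - CV^2*L*(1 - L) and L = 2.52/(2.52 + 0.58) = 0.813.

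| CV | DE, women weighted equally | Increase | Power | DE, efficient weighting | Power |
|---|---|---|---|---|---|
| 0 | 3.10 | – | 38.3% | 3.10 | 38.3% |
| 0.29 | 3.31 | 7% | 36.2% | 3.14 | 37.9% |
| 0.38 | 3.46 | 12% | 35.0% | 3.17 | 37.6% |
| 0.58 | 3.94 | 27% | 31.4% | 3.27 | 36.7% |

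For 80% power at d = 0.4, the requirement per arm is 99*3.10 = 307 with equal clusters, and 329 to 343 at CVs of 0.29 to 0.38. These figures show the size of the term; they are not a request to recruit.

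**Step 4: the same at smaller ICCs.** The article says its source "found the median value to be 0.01 for the HADS", with an interquartile range of 0 to 0.032.
- ICC 0.01: DE moves from 1.05 to at most 1.07; power from 81.5% to between 80.7% and 81.3%.
- ICC 0.032: DE moves from 1.16 to 1.18 or 1.19 (1.22 at the extreme); power from 77.5% to about 77% (75% at the extreme).

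**The case against.** Several points can be made for the plan, and most of them stand in part.

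- **Unequal sizes are not why 80% power is missed.** A reader might infer that they are. The documents do not support this: with every cluster at 6, power at the stated effect size and ICC is already about 38%. Correcting only the cluster-size term would leave the main errors in place. This stands, and it limits the point to a secondary one.
- **The plan does not claim that clusters are all of size 6.** It calls 6 an average. Using the mean alone is an approximation that is numerically equivalent to equal sizes; it is not an assertion of equal sizes. This also stands.
- **The limits 3 and 10 imply no particular CV.** No distribution of sizes is given, so any CV is an assumption. This is why a range is shown.
- **A fall from 80% to about 76% would overstate what the plan delivers.** That comparison takes the 80% at face value and needs an effect size of about 0.62, solved back from 41 per group. The article does not state that value; it states 0.4.
- **The loss shrinks if clusters are modelled.** With efficient weighting it is under 2 points even at the extreme CV. The article names no cluster term in its model, so it cannot be assumed that this smaller loss applies. Whether the model should have such a term is a separate question of validity.
- **The stated 2.6 leaves a margin at realistic ICCs.** It covers unequal clusters up to an ICC of (2.6 - 1)/(6*1.141 - 1) = 0.27 at CV 0.38, and 1.6/7 = 0.23 at the extreme. Both are far above the quoted upper quartile of 0.032. This is true, but the plan based its calculation on 0.42.

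It can also be said that a condensed article leaves such a refinement to the full protocol. However, the article prints both the formula and the cluster limits, and the two do not match.

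**Conclusion.** The point holds as a minor, additive error. At the plan's ICC of 0.42 the mean-only formula understates the design effect for a comparison that weights women equally: 3.10 becomes about 3.3 to 3.5 at CVs of 0.29 to 0.38, and 3.94 at the extreme. At d = 0.4 with 107 per arm this costs about 2 to 3 points of power (7 at the extreme), from a level that is already about 38%. The main causes of that level are the 41 per group and the factor 2.6.

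The size of the effect rests on the assumed CV, a two-sided test, no attrition and the ICC of 0.42. At the cited median ICC of 0.01 it is negligible.

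**What to change.** Correct the calculation under Statistical considerations in one pass:

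1. Replace the inflation factor by 1 + ((1 + CV^2)*m - 1)*ICC. State the CV as an assumption with a range (for example 0.29 to 0.38, with 0.58 as the extreme), or take it from the clusters already formed, since the article reports that recruitment is in progress.
2. In the same revision, give the unclustered n that follows from the stated effect size, and the factor that follows from the stated m and ICC. Without these, the cluster-size correction has little value.
3. Restate the design effect and the power that 214 women give, and show how both depend on the ICC.

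No further recruitment is asked for. The cost is a rewritten paragraph and a less favourable stated power.
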